**10.6** **Time point of analysis**

For the secondary outcome measures, MoCA-J and SF36 scores, data will be collected during the evaluation period and 6 months after the start of SoroTouch. For the primary outcome, CogEvo®︎, data will be collected during the evaluation period and every month thereafter until 6 months after the start of SoroTouch, and statistical analysis will be performed after the end of the observation period. If there are subjects whose average daily learning time is less than 10 minutes, in principle, the data will be analysed only for the period when they were able to perform the study for more than 10 minutes a day. However, all evaluated data should be used in the analysis. If necessary, subgroup analyses will be conducted according to medical history, diseases being suffered from, medications taken during the intervention period, etc.

The statistical analyst will compile a primary endpoint report and submit it to the principal investigator.

1. **Access to original data**

The principal investigator and the administrator of the implementing medical institution will accept monitoring and investigations by the accredited clinical research review committee and regulatory authorities on this research, and will ensure that all source documents and other materials related to this research are made available for direct inspection at that time.

1. **Quality control and quality assurance**

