**Intervention period （6 months）**

Control group（n = 10）

Enrolment

Informed consent

Random allocation

The principal investigator explains and obtains consent from the study subjects via online tools such as Zoom in order to prevent the spread of COVID-19 infection. The consent forms are converted into PDF format by the staff of the Consortium for Dementia Prevention Activities, and shared on a password-protected Dropbox and sent to the principal investigator. The paper consent forms are then promptly destroyed.

Schedule of the trials

| Evaluation item | **Registration to allocation should be done within 4 weeks. (Assessment allocation period)** | **One month after** | **Two months after** | **Three months after** | **Four months after** | **Five months after** | **Six months after** |
| --- | --- | --- | --- | --- | --- | --- | --- |
| Obtaining consents | ● |  |  |  |  |  |  |
| Investigation of Characteristics | ● |  |  |  |  |  |  |
| **MoCA-J** | ● |  |  |  |  |  | ● |
| SF36 | ● |  |  |  |  |  | ● |
| CogEvo^®︎^ | ● | ● | ● | ● | ● | ● | ● |
| Investigation of adverse events |  | | | | | | |

The participants will conduct the following curriculum in order from J1, as described in the user manual (Ref. 1). The participants will try to complete each stage, which has 30 missions, three aspects in 30 minutes each day.

The learning time is displayed on the SoroTouch recording screen and the learning time and mission completion status are checked by the staff of the Consortium for Dementia Prevention Activities.

If there are participants whose average daily learning time is less than 10 minutes, the data will be analyzed only for the periods when they were able to do more than 10 minutes.

Ref.1 SoroTouch curriculum

**
[figure not shown]
**

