**5.3** **Methods of case registration and allocation**

The principal investigator (co-investigator) explains the subject of the study in accordance with the explanatory document and, if consent is obtained, registers and allocates the subject as a research participant. Research participants will be given an identification code for anonymization purposes, which will be used as the identification code for research participants in this study.

The study will be conducted in a randomized comparison to ensure that the allocation does not result in differences in medical background between treatment groups. The participants will be allocated in a 1:1 ratio to the SoroTouch treatment group and the non-treatment group using Muzinwali (https://mujinwari.biz/users/login). The allocation method will be stratified block allocation with CogEvo®︎ (index below and above 70) as allocation factor. After obtaining consent from the study participants, investigators will access Muzinwali to confirm the allocation of the intervention to the study participants concerned. As soon as possible after confirming the allocation, the 'Allocation Instructions/Confirmation Form' is signed and dated. After obtaining consent from the research subject to participate in the research and conducting the allocation, the investigator in charge of the research should ensure that all 'allocation instructions/confirmation forms' are properly kept by the principal investigator.

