**10.1** **Subject of analysis**

10.1.1　 Subjects for efficacy analysis

All randomized subjects, excluding those with no intervention at all and those with no post-intervention assessments at all.

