**10.5.2** **Analysis of primary outcomes**

Group differences in change from baseline on the five cognitive domains (spatial cognition, orientation, memory, attention and executive function) scores of the CogEvo ®︎ will be assessed by analysis of covariance. The significance level is set at 0.05. Missing values are complemented by the last observed value.

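### Sections 5.2.2 and 10.6 cut low users' data to their adherent periods, 10.6 also says to use everything, and the unranked cut could filter only the app arm

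*Protocol*

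**What the plan says.** Three places in the Protocol bear on which data enter the analysis.

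- **Section 5.2.2**, after describing how staff check learning time, says that for participants averaging under 10 minutes a day "the data will be analyzed only for the periods when they were able to do more than 10 minutes". There is no hedge and no exception.
- **Section 10.6** repeats the rule, which now holds in principle only: "the data will be analysed only for the period when they were able to perform the study for more than 10 minutes a day". The next sentence is "However, all evaluated data should be used in the analysis".
- **Section 10.1.1** defines the efficacy set as "All randomized subjects, excluding those with no intervention at all and those with no post-intervention assessments at all". App use below a threshold is not a ground for exclusion.

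On measurement, 5.2.2 says "The learning time is displayed on the SoroTouch recording screen". On the comparator, 5.3 says participants are "allocated in a 1:1 ratio to the SoroTouch treatment group and the non-treatment group". The primary analysis in 10.5.2 compares changes from baseline: "scores of the CogEvo ®︎ will be assessed by analysis of covariance". The same section adds "Missing values are complemented by the last observed value", while 10.4 says that in principle missing values are not filled in.

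**The concern.** The protocol gives two instructions for the same records and ranks neither. Neither is called primary or supplementary, so the data set for the primary analysis is not settled. Analysis comes after observation ends (10.6), so the choice could be made with the data in hand.

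The restriction can act on one arm only. Control participants have no app and no learning time. Applied, it keeps or drops app-arm records according to what people did after randomisation, while every control record stays. The two sets of records are then no longer comparable by design.

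Two features add to this. If removed months count as missing, carrying the last value forward would replace a score that was actually measured with an earlier one; whether that happens is unclear, because 10.4 and 10.5.2 differ. And MoCA-J and SF36 have a single post-baseline assessment, at six months, so low use around that time could remove a participant's only follow-up value. Section 8.2.1 judges effectiveness by statistical significance with 10 per arm, so a few removed records could change the conclusion.

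**Working it through.** **1. The plan's own figure.** The rule has no stated figure. The nearest is the sample size in 10.2: effect size 1.4, type 1 error 0.05 (taken as two-sided), type 2 error 0.2, 20 participants. Normal approximation: n per arm = 2 × (1.960 + 0.842)² / 1.4² = 8.01, so 9 per arm, 18 in total. By the t-test, 9 per arm gives 79.6% power and 10 per arm 84.1%. Twenty is reproduced and is not in dispute.

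**2. Where bias would come from.** If a share p of app-arm records is removed, mean(kept) − mean(all) = p × δ, where δ is the mean of kept minus the mean of removed records. Assuming p = 0.2 to 0.3 and δ = 0.5 to 1.0 SD gives 0.2 × 0.5 = 0.10 to 0.3 × 1.0 = 0.30 SD. The sign is that of δ, which the documents do not give.

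**3. Simulation with no true effect.** From the protocol: 10 per arm, six monthly CogEvo visits, ANCOVA on change from baseline. Assumed:
- score = 0.7 × baseline + practice gain × month/6 + loading × monthly state + noise, with baseline SD 1 and residual variance 0.51;
- the monthly state also drives app use, with 70% or 50% of app-arm months adherent;
- the app arm is analysed at its last adherent month, controls at month 6, and app participants with no adherent month drop out.

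There were 1,500 runs per scenario. Cells show bias in baseline SD (positive favours the app) and rejection rate under the restriction.

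| Loading | Practice gain (SD) | 70% of months kept | 50% of months kept |
|---|---|---|---|
| 0 | 0 | -0.009; 4.9% | +0.005; 4.6% |
| 0 | 0.5 | -0.057; 5.2% | -0.055; 5.2% |
| 0 | 1.0 | -0.070; 5.9% | -0.146; 6.7% |
| 0.3 | 0 | +0.131; 7.3% | +0.200; 7.7% |
| 0.3 | 0.5 | +0.062; 5.0% | +0.135; 6.3% |
| 0.3 | 1.0 | +0.038; 5.1% | +0.060; 5.9% |
| 0.5 | 0 | +0.197; 7.3% | +0.343; 17.1% |
| 0.5 | 0.5 | +0.159; 8.3% | +0.258; 10.9% |
| 0.5 | 1.0 | +0.110; 5.9% | +0.199; 8.3% |
| 0.65 | 0 | +0.250; 11.9% | +0.460; 29.9% |
| 0.65 | 0.5 | +0.213; 10.3% | +0.374; 21.0% |
| 0.65 | 1.0 | +0.170; 7.5% | +0.306; 15.8% |

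With all evaluated data, bias ran from -0.017 to +0.009 SD and rejection from 4.1% to 5.9%. The Monte Carlo standard error at 5% is √(0.05 × 0.95 / 1,500) = 0.56 points, so this is nominal.

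**4. A limit of the simulation.** It filters every app participant month by month. The protocol's rule is triggered per person, by an average below 10 minutes, so someone above the threshold keeps even weak months. If each affected person keeps half their months, removing 30% to 50% of app-arm months needs 0.3/0.5 × 10 = 6 to 0.5/0.5 × 10 = 10 of the 10 app participants below the threshold. With fewer low users the bias would be smaller.

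**5. Loss of participants.** If app participants with no adherent period drop out, the noncentrality 1.4 / √(1/n₁ + 1/n₂) falls from 3.13 (10 v 10) to 2.95 (8 v 10) or 2.71 (6 v 10). Power falls from 84.1% to 79.1% or 71.3%.

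**The case against.** The best defence is that 10.6 resolves itself. The restriction there holds only in principle, and the sentence beginning with a contrast can be read as overriding it. That fits the efficacy set in 10.1.1, and under that reading the rule causes no bias. This stands as a possible reading, but it leaves 5.2.2, which has neither the hedge nor the second sentence, in open conflict with 10.6.

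A reader might infer that the comparison is biased, and biased towards the app. The documents do not support either as fact. Bias arises only if the restriction governs. That low users are those with lower or declining function is an assumption: 6.2 describes healthy people, and 6.4 lists a busy schedule among reasons for leaving. A practice gain over monthly testing could push the bias the other way.

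A reader might also infer that the rule, taken literally, deletes all control data. That is strained: 5.2.2 ties the rule to the app's recording screen, so controls have no learning time rather than a low one.

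Two safeguards help in part. Section 10.3 provides for a review of subjects before analysis, and section 10 requires a protocol revision if the analysis plan changes. Neither says which rule applies or that the review is blinded. The study is exploratory (section 4 and 10.2), which limits the stakes, but 8.2.1 still bases an effectiveness claim on significance.

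**Conclusion.** The point holds in this form: the protocol fixes two incompatible rules for the data entering the analysis and does not rank them. One of them, if applied, selects app-arm data on adherence after randomisation while control data stay whole. The conflict is in the text and rests on no assumption; the bias is conditional on the restriction being used.

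Size and direction cannot be read from the documents, which give no adherence rate and no link between use and score. Over the assumed scenarios the bias ran from about -0.15 to +0.46 SD. Where use was linked to score, it was +0.04 to +0.46 SD with type 1 error of about 5% to 30%, the upper end needing a strong link and half of app-arm months removed. With a practice gain but no link, it was about -0.06 to -0.15 SD. With neither, there was none.

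**What to change.** - In 5.2.2 and 10.6, remove the 10-minute restriction as a rule for the primary and secondary analyses. State that these use all evaluated data, by allocated arm, whatever the learning time.
- Align this with 10.1.1 so that the sections describe one analysis set, and say there that low app use is not a ground for exclusion.
- Keep the 10-minute cut, if wanted, only as a labelled supplementary analysis, and report learning time descriptively in the app arm.

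The cost is a wording change in three sections and the review committee approval that 22.2 requires. No participants or visits are added, and power at an effect size of 1.4 stays at 84.1% with 10 per arm analysed. The downside is that the estimate may be diluted by non-use, which the supplementary analysis can help to show. The change does not recover data from participants whose observation stops under 6.4; that is a separate matter on which this point proposes nothing.

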5.2.2 Clinical research flow/outline

Registration to allocation should be done within 4 weeks. (Assessment allocation period).

Intervention group（n = 10）

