**5.8　Contents directly entered in the case report form and considered source documents**

In this study, the following documents and others are considered source documents (source data).

1) Records of research participant consent and information provided to participants.

2) Information on the presence or absence of diseases, history of diseases, medications taken, etc., as stated in the monitoring application form.

3) Documents or records relating to trials required under the Clinical Research Act in relation to the study.

1. **The inclusion and exclusion criteria and discontinuation criteria for the clinical research**

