**6.3　Exclusion criteria**

The subjects must not meet all of the following criteria.

1) Persons with visual or intellectual disabilities that make it difficult to perform SoroTouch.

(2) Persons who have been administered drugs that affect the results of the study to treat dementia or ADHD within six months.

(3) Individuals who are judged to be ineligible by the physician in charge of the study.

[Rationale for setting exclusion criteria.]

(1) Individuals with visual impairment or intellectual disability are difficult to perform the SoroTouch.

(2) Use of drugs that affect cognitive function, as this will affect the results of the study.

3) People who are clearly clinically inappropriate to participate in the study should not participate.

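### One optional subgroup factor in Protocol 10.6, medication taken during the intervention, is observed after randomisation and should be defined before allocation (minor)

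*Protocol*

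**What the plan says.** Protocol 10.6 ends its account of the analysis with: "If necessary, subgroup analyses will be conducted according to medical history, diseases being suffered from, medications taken during the intervention period, etc". The analysis is therefore optional, the list is open, and "medications taken during the intervention period" is one of its items.

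Allocation comes before the six-month intervention period (5.2.2). Participants are "allocated in a 1:1 ratio to the SoroTouch treatment group and the non-treatment group" (5.3), and the method is "stratified block allocation with CogEvo®︎ (index below and above 70) as allocation factor". Medication is not an allocation factor.

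On where medication data come from, 5.8 lists as a source document: "Information on the presence or absence of diseases, history of diseases, medications taken, etc., as stated in the monitoring application form". It does not say when that form is completed. The schedule in 5.2.2 marks the investigation of characteristics only in the pre-allocation column and has no row for medication at later visits.

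Section 6.3 excludes "Persons who have been administered drugs that affect the results of the study to treat dementia or ADHD within six months", and its rationale says that drugs affecting cognitive function will affect the results.

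**The concern.** A subgroup comparison keeps the protection of randomisation when the subgroup is fixed before allocation. Medication taken during the intervention is not fixed then. If being in one arm changes who takes a drug, or whose drug use is recorded, and drug takers differ in prognosis, then users in one arm are a different kind of person from users in the other. The same holds for non-users. A group difference can then appear in both subgroups with no treatment effect, or a real one can be hidden.

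The document makes an effect of arm on medication possible, though it does not show one. The comparator is no treatment, so participants can be expected to know their group. Staff check learning time and mission completion in the SoroTouch arm (5.2.2), with no counterpart described for controls. Help-seeking and recording could differ. The protocol itself regards some drugs as affecting the results.

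At stake is the reading of an exploratory subgroup result. This kind of bias does not shrink as the sample grows, so the definition should not be copied unchanged into the larger study foreseen in 10.2.

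**Working it through.** **The plan's own figure.** Section 10.2 gives 20 subjects for an effect size of 1.4, Type 1 error 0.05 and Type 2 error 0.2. A two-sided two-sample t-test needs 9.08 per arm, hence 10 per arm and 20 in total, with power 0.84. The figure reproduces. It does not bear on the subgroup definition, for which the protocol gives no number.

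**Order of events.** Registration and assessment, then allocation (5.2.2, 5.3), then the six-month intervention, then subgroups formed by medication in that period (10.6). No section limits the factor to medication at entry.

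**Size under a simple model (all inputs assumed).** There is no treatment effect. A latent poor course correlates 0.7 with starting a drug and 0.5 with a worse outcome, so the combined correlation is r = 0.7 × 0.5 = 0.35. Drug starters are 40% of controls and 20% of the SoroTouch arm. Start is a threshold on a normal variable, with p the proportion starting, z the threshold and φ the normal density. The outcome is in SD units, higher being better.

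- Mean outcome in users = -r × φ(z)/p
- Mean outcome in non-users = +r × φ(z)/(1 - p)

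| | Control, p = 0.40 | SoroTouch, p = 0.20 |
|---|---|---|
| z | 0.253 | 0.842 |
| φ(z) | 0.386 | 0.280 |
| φ(z)/p | 0.966 | 1.400 |
| φ(z)/(1 - p) | 0.644 | 0.350 |

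- Users: -0.35 × (1.400 - 0.966) = -0.15 SD
- Non-users: 0.35 × (0.350 - 0.644) = -0.10 SD
- Whole sample: 0, because within each arm the user and non-user means cancel when weighted by p and 1 - p

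A simulation of the same scenario gave -0.150, -0.104 and 0.000. The result is proportional to r: at r = 0.5 it would be -0.5 × 0.434 = -0.22 SD in users and -0.5 × 0.294 = -0.15 SD in non-users. If the SoroTouch arm had more starters than controls, the sign would reverse.

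**A second model, 2,000,000 simulated subjects.** There is no treatment effect, the outcome correlates 0.5 with a latent prognosis U, and logit P(use) = -0.5 - U + b × arm, with arm = 1 for SoroTouch.

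| b | Use, control | Use, SoroTouch | False difference, users | False difference, non-users |
|---|---|---|---|---|
| 0 | 40% | 40% | 0.00 | 0.00 |
| -0.5 | 40% | 30% | -0.05 | -0.03 |
| -1 | 40% | 22% | -0.09 | -0.07 |
| -1.5 | 40% | 16% | -0.12 | -0.09 |
| -2 | 40% | 11% | -0.16 | -0.11 |

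The whole-sample difference was 0.002 throughout, which is simulation noise. The first row shows that the bias needs an effect of arm on use.

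**Set against sampling error.** With outcome SD 1, the standard error of a difference is √(1/n1 + 1/n2).

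- 30% users in each arm of 10, so 3 and 3: √(2/3) = 0.82 SD
- Users at 40% and 20%, so 4 and 2: √(1/4 + 1/2) = 0.87 SD
- Non-users, 6 and 8: √(1/6 + 1/8) = 0.54 SD

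The bias is 0.15/0.87 = 0.17 of a standard error in users and 0.10/0.54 = 0.19 in non-users. For an effect of 1.4, t-test power is 0.49, 0.38 and 0.26 with 5, 4 and 3 per arm.

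**The case against.** The other side has a strong case on weight. The bias needs two links: from arm to medication use, and from use to prognosis. The protocol gives no drug-start rates and no reason why a mental-arithmetic app should change prescribing. Participants are meant to be healthy community adults. If medication is mostly continued from entry, these are in effect baseline subgroups and there is no bias. With about 3 people per arm, noise is several times larger than any of the figures above, and a baseline definition does not cure that. All of this stands, and it sets the severity.

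A reader might infer that this is the plan's only subgroup analysis, and that all of it is compromised. The text does not support that. It is one item in an optional, open list. Medical history is a baseline factor, and current disease is only ambiguous as to timing.

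A reader might also infer that entry medication is certainly on file, so that the change needs no new data and loses nothing. Section 5.8 does not date the monitoring application form, and the schedule does not name medication. The loss is not zero either: section 6.3 excludes recent users of dementia or ADHD drugs, so a baseline subgroup should contain essentially none of them. If the item was meant as a check on drugs started in follow-up, that check becomes descriptive.

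What the objection does not remove is the wording. Section 10.6 names a post-allocation variable, nothing elsewhere limits it to baseline, and section 10 says that a change to the analysis plan requires the protocol to be revised.

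**Conclusion.** The point holds as a minor fault in a stated rule. Subgroups formed by medication during the intervention are not protected by randomisation if allocation influences use and use relates to prognosis. Under assumed rates the false difference runs from about 0 to roughly -0.15 SD, or somewhat more with stronger links. The central case is about a tenth of the 1.4 SD effect in 10.2 (0.15/1.4 = 0.11) and less than a fifth of the subgroup's standard error.

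It would be wrong to infer that the trial's main results are affected. The analysis of covariance in 10.5.2 and the comparisons in 10.5.3 do not use this variable. Nor does 10.2 say that optional medication subgroups will shape the larger study; it refers to the results on cognitive function and quality of life.

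**What to change.** In 10.6, define the medication subgroup, and the one by current disease, by status recorded before allocation. The source could be the pre-allocation investigation of characteristics, or the monitoring application form if it is completed at entry; the protocol should say which. Report group-by-subgroup estimates with confidence intervals, labelled exploratory. Describe any medication started during the intervention by arm, to the extent it is recorded, and form no subgroups from it.

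The cost is mainly a wording change, plus a check that medication is in fact recorded before allocation. The small downside is that drugs started during follow-up are described and not examined as a subgroup. If they are to be listed fully, their collection has to be confirmed, since the schedule in 5.2.2 shows none.
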